### Inclusion criteria

The criteria for inclusion into the interventional and observational cohorts are shown in Table 3.

**Table 3 Tab3:** Inclusion criteria for the interventional and observational cohorts of the RIBBS study

	Interventional cohort	Observational cohort
Female	X	X
45-year-old	X	X
Resident in defined provinces of the two regions	X	X
Willing and able to give written informed consent	X	NA
Willing and able to comply with scheduled visits, tests, and other procedures	X	NA

NA, Not Applicable. In the interventional cohort, ethics committee approval and the signing of an informed consent form by each participating woman was required. The observational cohort is derived from a population-based screening programme, in which participation is considered indicative of consent

### Exclusion criteria

The exclusion criteria for both cohorts are shown in Table 4.

**Table 4 Tab4:** Exclusion criteria for the interventional and observational cohorts of the RIBBS study

	Interventional cohort	Observational cohort
Recent mammography	X	X
Personal history of invasive breast cancer and ductal carcinoma in situ		
	X	X
Known or suspected germline mutation of BRCA1/2, PALB2, TP53 or equivalent	X	X
Psychiatric and other disorders not compatible with compliance to the protocol requirements and follow-up	X	X
Pregnancy or breastfeeding	X	X
Unable to give informed consent	X	NA
Current participation in another breast screening trial	X	NA

NA: Not Applicable. In the interventional cohort, ethics committee approval and the signing of an informed consent form by each participating woman was required. The observational cohort is derived from a population-based screening program, in which participation is considered indicative of consent

### Data collection and management

Data collection and management will adhere to general Italian data protection regulations, ensuring maximum privacy and security of participants' information.

For the interventional cohort, a database dedicated to the RIBBS study was developed. This repository includes several tables containing essential information, such as mean VBD, calculated with the Volpara software, individual risk factors included in the IBIS software for lifetime risk assessment based on the Tyrer-Cuzick risk model, recall data derived from double readings, and details obtained from any required diagnostic procedure, including histologic data from biopsies. The raw data will be accessible for a variety of analyses or subanalyses.

As regards the observational control cohort, primary records will be obtained from the Emilia-Romagna Region mammography screening data warehouse. These data provide comprehensive information on invitations, mammograms, diagnostic procedures for abnormal screening outcomes, and benign or malignant lesions detected by screening. The case series is linked with the population-based regional breast cancer registry to obtain additional information.

To identify incident cases of breast cancer, all women in the interventional and observational control cohorts will be linked to the Veneto and Emilia-Romagna Cancer Registries, respectively. Automated case registration through the Veneto Cancer Registry has recently demonstrated a high level of consistency and reliability [49]. Previous studies have also validated the record-linkage protocols in both registries [38, 50]. Primary information available from both registries includes sociodemographic characteristics, primary cancer site, TNM tumour stage, histologic type, and vital status.

### Sample size

Sample size calculations focused specifically on the primary outcome measure of the personalized screening procedure. This primary outcome measure revolves around assessing the reduction in the incidence of advanced breast cancer in the interventional cohort compared with the observational control cohort.

Considering the real-world context of the study and the constraints associated with enrolling participants in both cohorts, the sample size calculations encountered some limitations. The enrollment of patients in both cohorts was limited by factors such as available space and tight timelines due to the initial approval period granted by the Veneto Region. This consequently prevented expansion of the cohorts beyond the approved period.

Given the impossibility of accurately determining the sample size required to detect a specific effect on the primary outcome with the desired statistical power, our approach involved estimating the minimum detectable reduction in the incidence of advanced BCs using the sample size provided and ensuring a minimum power of 80%. The sample sizes available to conduct a one-sided test comparing the null hypothesis H0: rate ratio ≥ 1.000 and the alternative Ha: rate ratio < 1.000, using the W5 Variance Stabilized test statistic, were determined in 43,000 subjects in the observational control cohort and 10,269 subjects in the total interventional screening cohort, both over a 5-year exposure period. With these designated sample sizes, the study is able to achieve a power of 80.5% in detecting an event rate ratio under the alternative hipothesis (RRa) of 0.810. The event rate in the observational control cohort (λ1) is estimated to be 0.004017, based on the incidence rate of BC at baseline. Specifically, the significance level (alpha) used in the test is 0.050.

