### Statistical analysis

Regarding the primary objective of the study, which focuses on evaluating the impact of the personalized screening model on the cumulative incidence of advanced breast cancer (stage II or higher), a series of analyses are planned. Person-years at risk and follow-up duration will be calculated for both cohorts, starting from the date of first screening and continuing until the date of censoring or the end of follow-up, whichever comes first. The follow-up duration will be truncated at the 75th percentile of available follow-up times, as determined by the criterion proposed by Puliti et al. [51].

Woman age will be calculated at the date of the first screening. Cumulative age-standardized advanced breast cancer incidence rates will be calculated for both cohorts and then compared using the incidence rate ratio (IRR) along with 95% confidence interval (95% CI). Estimation of IRRs will be obtained by multivariable Poisson regression analysis.

To address potential dissimilarities (if any) in the risk of breast cancer between the two cohorts, incidence rates from the pre-intervention period will be used. Adjusting the IRR of advanced breast cancer will involve multiplying the unadjusted IRRs by the observed/expected ratio within the observational control cohort. Calculation of 95% CIs will be performed by a bootstrap procedure.

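### The stated 80.5% power belongs to a one-sided 5% test of the unadjusted rate ratio; for the planned 95% interval on the baseline-adjusted ratio, power at 0.81 is at most about 70–73%

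*Protocol article*

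**What the plan says.** Protocol article, Sample size. The cohorts were fixed by circumstances, so the authors give the smallest reduction detectable with at least 80% power. The calculation is introduced with the words "The sample sizes available to conduct a one-sided test comparing the null hypothesis"; the null is a ratio of at least 1 and the alternative a ratio below 1. The method is given as "using the W5 Variance Stabilized test statistic". The numbers entered are "43,000 subjects in the observational control cohort and 10,269 subjects in the total interventional screening cohort", with five years of exposure assumed for each woman and a control event rate of 0.004017. It adds that "the significance level (alpha) used in the test is 0.050" and arrives at 80.5% power at a rate ratio of 0.810. Nothing in it refers to the baseline adjustment.

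Protocol article, Statistical analysis. The cohorts are to be compared by an IRR from Poisson regression with a 95% confidence interval. The IRR is then corrected for pre-intervention differences in risk by multiplying it by an observed-to-expected ratio from the control cohort. "Calculation of 95% CIs will be performed by a bootstrap procedure".

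Study design describes the between-cohort ratio as adjusted for baseline incidence, and Study limitations offers that adjustment as the answer to bias from non-randomised allocation. The adjusted ratio is therefore the main comparison.

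**The concern.** The power statement and the planned analysis differ in two ways.

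1. **Error level.** A one-sided 5% test corresponds to a two-sided 90% interval. The 95% interval corresponds to 2.5% in the favourable direction.
2. **Quantity tested.** The power calculation contains the sampling error of two follow-up counts only. The adjusted IRR also carries the sampling error of a ratio estimated from finite pre-period counts.

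Both differences push the same way, so 80.5% overstates the chance that the planned interval excludes 1 when the true ratio is 0.81. A reader who sees an interval that includes 1 would also misjudge how informative that result is. In addition, the test and the interval can disagree over a narrow range of results, and the article does not say which one governs.

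**Working it through.** **Inputs from the Sample size section.** 43,000 and 10,269 women, 5 years each, control rate 0.004017, rate ratio 0.81, one-sided alpha 0.05.

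**Step 1: reproduce the stated power.**
- Control events: 43,000 × 5 × 0.004017 = 863.7.
- Intervention events: 10,269 × 5 × 0.004017 × 0.81 = 167.1.
- Log scale: SE = √(1/863.7 + 1/167.1) = 0.0845 and |ln 0.81| = 0.2107. Power = Φ(0.2107/0.0845 − 1.645) = 80.2%.
- W5 (square roots with 3/8 added): [√(864.0 × 10,269/43,000) − √167.4] / [0.5 × √(1 + 10,269/43,000)] = (14.365 − 12.940)/0.5565 = 2.56. Power = Φ(2.56 − 1.645) = 82.0%.

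The two results bracket or closely match the stated 80.5%. Reading 0.004017 as a 5-year cumulative risk gives only about 30%, so it was used as an annual rate.

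**Step 2: require the 95% interval to exclude 1, still unadjusted.** Only the critical value changes, to 1.96.
- Log scale: Φ(0.2107/0.0845 − 1.96) = 70.3%.
- W5: Φ(2.56 − 1.96) = 72.6%.
- Ratio detectable with 80% power: exp[−(1.96 + 0.8416) × 0.0845] = 0.79. With 1.645 in place of 1.96 it is 0.81, as stated.
- Zone of disagreement: exp(−1.96 × 0.0845) = 0.85 to exp(−1.645 × 0.0845) = 0.87. An observed unadjusted ratio in this range is significant one-sided at 5% while its 95% interval includes 1.

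This step needs no input from outside the document.

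**Step 3: add sampling error in the baseline ratio.** Treating the adjustment approximately as a ratio of two rate ratios, SE = √(1/863.7 + 1/167.1 + 1/B_V + 1/B_ER), where B_V and B_ER are the pre-period event counts in Veneto and Emilia-Romagna. The article gives neither count, so what follows is assumption.
- Veneto: about 10,000 women per year of age (Context) × 5 ages (Study design) × 3 years (Pre-screening and screening periods) = 150,000 person-years. × 0.004017 = 603 events.
- Emilia-Romagna: varied from 100,000 to 300,000 person-years.

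| Emilia-Romagna person-years | Events | SE | Power, 95% interval | Power, one-sided 5% | Detectable ratio, 95% interval |
|---|---|---|---|---|---|
| 100,000 | 402 | 0.1063 | 51% | 63% | 0.74 |
| 200,000 | 803 | 0.1002 | 56% | 68% | 0.755 |
| 300,000 | 1,205 | 0.0981 | 57% | 69% | 0.76 |

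Cross-check on the Emilia-Romagna range: Study status gives 43,840 participants over 2012–2020, or about 4,871 a year. × 5 ages × 5 years gives 489 events if all residents took part and 978 if half did. Power is then 52.5% to 56.6% (simulation: 53% to 57%).

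**Step 4: sensitivity of Step 3 to the baseline (95% interval).**
- 1,000 Veneto and 2,000 Emilia-Romagna events: 62%. 2,000 and 4,000: 66%.
- Only the control cohort's baseline carries error, 489 or 864 events: 59% or 64%.
- Only advanced cancers counted at baseline, assumed to be 35–50% of cases: 35–42%.
- Age 45 only (98 and 121 events): 26%.
- Baseline ratio treated as known: 70–73%, as in Step 2.

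**The case against.** The Sample size section is candid that numbers were fixed by circumstances, and it presents a detectable effect rather than a justification for recruiting. Enrolment is closed, so no design decision now turns on 80.5%. The hypothesis is directional, which makes a one-sided test a legitimate choice, and a decision rule may stand in a document not shown here. Follow-up runs to at least 10 years, whereas every figure above is for the 5-year exposure used in the calculation. All of this stands. It limits the consequence but does not make 80.5% the power of the analysis that the article describes.

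Three stronger readings are tempting and are not supported.

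- **That the true power is 51–57%.** This rests on assumed pre-period person-years and on a bootstrap that carries baseline error. The article does not state the counts, how the expected number is formed, or what is resampled. Study design speaks of the ratio between the two regions. If whole-region registry rates were used, the counts would be larger and power would move back towards 70–73%.
- **That harm could not be detected.** The one-sided hypothesis gives no formal test for harm, but the planned 95% interval would show it by a lower limit above 1. Wanting a formal harm rule is a preference, not an error in the plan.
- **That superiority will be claimed on an interval that includes 1.** The article names no success rule. The conflict is possible between about 0.85 and 0.87, but nothing shows it would be resolved that way.

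**Conclusion.** The mismatch is real and can be seen in the text. With the protocol's own inputs, and success defined as an upper 95% limit below 1, power at a ratio of 0.81 is about 70–73%, and the ratio detectable with 80% power is about 0.79. That part is firm. Any baseline error carried into the interval lowers power further. The direction is certain; the size is not. The 51–57% is one scenario (150,000 Veneto and 100,000–300,000 Emilia-Romagna person-years, all breast cancers counted), larger baselines give 62–66%, and narrower ones give less. Every variant is below 80.5%. All figures keep the stated event rate, which the Sample size section attributes to breast cancer incidence at baseline although the outcome is stage II or higher; a lower rate for advanced cancer would reduce them all. This should be corrected, but it does not prevent the estimate from being computed.

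**What to change.** - State one decision rule tied to the reported interval of the baseline-adjusted IRR. Either superiority requires the upper limit of the two-sided 95% interval to be below 1, or, if the one-sided 5% test is kept, report the interval that matches it (two-sided 90%).
- State that the bootstrap resamples the pre-period counts as well as the follow-up counts.
- Restate power and the minimum detectable ratio for that rule, using the actual registry baseline counts. The sum of the reciprocals of the four event counts is an adequate approximation to the log-scale variance, to be replaced if the observed-to-expected ratio is built differently.

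The cost is a recalculation and a few sentences. The stated power will be lower or the detectable effect larger. Nothing changes in enrolment, screening or data collection.

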### Outcome measures

The primary and secondary outcome measures are listed in Table 1. The primary measure of the effectiveness of screening stratified by breast density and risk, compared with conventional annual mammography, will be the cumulative incidence of advanced breast cancer. In particular, the focus will be on stage II or higher cancer throughout the follow-up period. Most of the secondary outcome measures are part of the core indicators used in the annual national survey of regional mammography screening programmes in Italy. These indicators were defined by the Italian Group for Mammography Screening and the Italian National Centre for Screening Monitoring [48]. They constitute the benchmark for reporting outcomes of breast cancer screening programmes in Italy.

**Table 1 Tab1:** Primary and secondary outcome measures in the RIBBS study

	Description
Primary outcome meausure: cumulative incidence of advanced breast cancer	Measure of effectiveness of screening stratified by breast density and risk compared with standard annual digital mammography. Focuses on stage II or higher cancer throughout the follow-up period
Secondary outcome measures	
Recall rate	Number of women recalled for further diagnostic evaluation per thousand women undergoing each of the two screening protocols
Cancer detection rate	Number of women with breast cancer detected by screening (topographic code C50 [47]) per thousand women undergoing each of the two screening protocols
Proportional incidence of interval cancer	Number of women diagnosed with interval cancer (detected after a negative screening episode) divided by the expected number of breast cancer cases in the absence of screening, by screening protocol and interval year
Total assessment rate	Number of women undergoing diagnostic evaluation per thousand women undergoing each of the two screening models, further subdivided into non-invasive and invasive assessment rates
Surgical referral rate	Number of women referred for excisional biopsy or definitive surgical treatment per thousand women undergoing each of the two screening protocols
Surgery rate	Number of women undergoing excisional biopsy or definitive surgical treatment per thousand women undergoing each of the two screening protocols
Benign lesion detection rate	Number of women with any histologically diagnosed benign lesion per thousand women undergoing each of the two screening protocols

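### The 80.5% five-year power is stated for advanced (stage II+) breast cancer but rests on a control rate described as breast cancer incidence without stage

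*Protocol article*

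**What the plan says.** The Sample size section says that its calculations concern the primary outcome, the reduction in advanced breast cancer. Because the cohort sizes were fixed by circumstances, it reports a minimum detectable reduction at no less than 80% power. Under Outcome measures the endpoint is specified: "In particular, the focus will be on stage II or higher cancer throughout the follow-up period". Statistical analysis repeats the stage II or higher definition.

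The hypotheses are set up as a "one-sided test comparing the null hypothesis H0: rate ratio ≥ 1.000 and the alternative Ha: rate ratio < 1.000". The statistic named for it is W5, a variance-stabilised form. The cohorts are "43,000 subjects in the observational control cohort and 10,269 subjects in the total interventional screening cohort, both over a 5-year exposure period", and "the significance level (alpha) used in the test is 0.050". The result is that the study can "achieve a power of 80.5% in detecting an event rate ratio under the alternative hipothesis (RRa) of 0.810". The control event rate (λ1) behind it "is estimated to be 0.004017, based on the incidence rate of BC at baseline".

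The Abbreviations expand BC as breast cancer, with no mention of stage. The Study design section says that the pre-screening phase measures baseline breast cancer incidence in women aged 45–49. Only for the screening period does it speak of advanced breast cancer. Pre-screening and screening periods dates the control baseline to 2005–2009, before the annual programme reached this age group.

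**The concern.** The endpoint and the event rate do not match. The power claim is made for stage II+ cancer, but the rate put into it is described as the incidence of breast cancer as such. Only part of that incidence can be stage II+. The planned secondary outcome of stage-specific detection rates shows that the investigators expect a range of stages. With fewer events than assumed, power at a rate ratio of 0.81 is lower and the detectable reduction is larger than the 19% stated.

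The cohort sizes cannot change, so the minimum detectable effect is the one product of this paragraph. If it was computed for a different endpoint, a null or imprecise five-year result could be read as evidence against a 19% reduction when the comparison had too few stage II+ events to show one.

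**Working it through.** **Inputs (Sample size section).** Control n₁ = 43,000; interventional n₂ = 10,269; t = 5 years; λ1 = 0.004017; RR = 0.81; one-sided α = 0.05, so z = 1.645. Exposure ratio d = 43,000/10,269 = 4.187.

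**1. Reproducing the stated power, with λ1 per woman-year.**

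Control events: E₁ = 0.004017 × 5 × 43,000 = 863.7. Interventional events: E₂ = 0.004017 × 0.81 × 5 × 10,269 = 167.1.

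- W5: A = 2[√(E₁ + 3/8) − √(d(E₂ + 3/8))]/√(1 + d) = 2(29.394 − 26.479)/2.278 = 2.560. Power = Φ(2.560 − 1.645) = 82.0%. A simulation with 400,000 draws gives 82.5%.
- Log-rate scale: |ln 0.81| = 0.2107; SE = √(1/863.7 + 1/167.1) = 0.0845. Power = Φ(0.2107/0.0845 − 1.645) = 80.2%.

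The stated 80.5% lies between these two figures.

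**2. Other readings of the inputs do not reproduce it.** If 0.004017 is a five-year cumulative rate, events are 172.7 and 33.4 and power is about 30%. A two-sided 5% test with the annual rate gives 73% (W5) or 70% (log scale). So the stated figure needs the full rate, applied annually, with a one-sided test.

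**3. What that implies.** 863.7/43,000 = 2.0% of control women would be counted as having stage II+ cancer within five years.

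**4. Power for the named endpoint.** Let f be the stage II+ rate as a share of 0.004017. The documents do not give f, so every value below is an assumption. The formula is W5 with λ1 = f × 0.004017, over five years.

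| f (assumed) | Control events | Interventional events at RR 0.81 | Power at RR 0.81 | RR detectable with 80.5% power |
|---|---|---|---|---|
| 25% | 216 | 42 | 35% | 0.64 |
| 33% | 285 | 55 | 42% | 0.69 |
| 50% | 432 | 84 | 56% | 0.74 |
| 60% | 518 | 100 | 63% | 0.76 |
| 80% | 691 | 134 | 74% | 0.79 |
| 100% | 864 | 167 | 82% | 0.81 |

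Simulation at f = 25% and 50% gives 35.3% and 56.6%.

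**5. Threshold.** W5 power at RR 0.81 is 79.8% at f = 0.94 and 80.2% at f = 0.95, and it crosses 80% at f ≈ 0.944. The log-rate formula is stricter, because it gives only 80.2% with the full rate.

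**The case against.** **Wording slip.** The word for advanced may simply have been dropped before BC, since the section opens by naming the primary outcome. The article condenses a fuller protocol that is not shown, so the source of λ1 cannot be checked. This cannot be excluded, and it is why the authors should first state what λ1 is. The text counts against it: the same paragraph writes advanced BCs when it means advanced disease, and Study design describes the baseline as breast cancer incidence. The 2.0% in five years would also be a stage II+ figure for an annually screened cohort. It looks high, but the documents offer no benchmark, so it is not proof.

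**Inexact reproduction.** W5 gives 82.0%, not 80.5%. The match is close enough to identify an annual rate applied in full, but it is not exact.

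**Size and horizon.** A reader might infer that power for the primary outcome is 35–56%. The documents do not support that as a general statement. The range needs an assumed share of 25–50%, and nothing in the article caps the share at 50%. It also covers five years only, while comparisons are planned at three, five and ten years. With a constant rate and rate ratio, ten years doubles the events, and W5 power becomes about 56%, 67% and 82% at shares of 25%, 33% and 50%. That is illustrative, because both cohorts move to biennial mammography at 50 and the effect may dilute. Longer follow-up does not repair a figure stated for five years.

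**Limited consequence.** Enrolment is complete, the section admits its constraints, and the analysis reports rate ratios with 95% confidence intervals, so imprecision will be visible. This stands and limits the harm. The admitted constraints concern cohort size, however, and do not disclose an event rate for a different endpoint.

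**Conclusion.** The power statement is wrong as written. It is presented for stage II+ cancer but uses a rate described as pre-screening breast cancer incidence without stage, and it reproduces only when that full rate is applied annually for five years.

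The direction hardly depends on assumptions: by W5, five-year power at a rate ratio of 0.81 is below 80% unless the stage II+ rate is about 94% or more of 0.004017. The size does depend on them. It runs from about 35% at an assumed share of 25% to about 74% at 80%, and the documents do not say where in that range the study lies. What they support is a five-year power below the stated 80% by an amount still to be determined.

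Taking the rate from before screening is a further mismatch. Study design cites a fall in pT2-4 cancers from the third year of screening, so the rate in the annually screened controls may be lower still. The conclusion does not need this point.

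**What to change.** State the stage definition and time unit of λ1. Replace it with the annual stage II+ rate observed in the Emilia-Romagna cohort under annual screening. Data collection and management says that the cohort is linked to the regional cancer registry and that TNM stage is available. Then restate, for 43,000 and 10,269 women over five years, the one-sided power at a rate ratio of 0.81 and the minimum detectable rate ratio.

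The cost is one registry tabulation and a rewritten paragraph, with no extra enrolment and no change to the endpoint or the analysis. The downside is that the stated power, or the detectable effect, becomes less favourable.
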